### Outcome measures

#### Primary outcome

The primary outcome is mean change in HbA_1c_ level at Month 12 from baseline. Decreases in HbA_1c_ level have been associated with risk reductions in diabetes-related clinical complications or mortality, and diabetes randomized trials frequently use mean reduction in HbA_1c_ level as a study outcome [5, 25].

#### Secondary outcomes

The secondary outcomes are:
Mean change in HbA_1c_ level at Months 6, 18, and 24 from baselineMean change in weight at Months 6, 12, 18, and 24 from baselineMean change in systolic and diastolic blood pressure at Months 6, 12, 18, and 24 from baselineProportion of participants who had insulin treatment initiated by their diabetes care physician by Months 6, 12, 18, and 24Mean change in self-reported physical activity at Months 6, 12, 18, and 24 from baseline as assessed using the Global Physical Activity Questionnaire (GPAQ) [26]Mean change in self-reported weight monitoring at Months 6, 12, 18, and 24 from baseline as assessed by frequency of self-weighingMean change in self-reported blood glucose monitoring at Months 6, 12, 18, and 24 from baseline as assessed by frequency of self-testingMean change in self-reported medication adherence at Months 6, 12, 18, and 24 from baseline as assessed by frequency of taking diabetes medications as prescribedMean change in diabetes self-management at Months 6, 12, 18, and 24 from baseline as assessed using the Diabetes Self-Management Questionnaire (DSMQ) [27]Mean change in sleep quality at Months 6, 12, 18, and 24 from baseline as assessed using the Pittsburgh Sleep Quality Index (PSQI) [28]Mean change in work productivity and daily activity impairment at Months 6, 12, 18, and 24 from baseline as assessed using a modified Work Productivity and Activity Impairment: Specific Health Problem instrument (WPAI:SHP) [29]Mean change in health utility index at Months 6, 12, 18, and 24 from baseline as assessed using the 5-level EQ-5D instrument [30]ICERs based on HbA_1c_ level, determined by calculating the incremental cost per percentage point unit reduction in HbA_1c_ level at Month 12 (primary endpoint)ICERs based on QALYs, determined by converting ICER based on HbA_1c_ level into incremental cost per QALY gained.

### Sample size

Data from Bilger et al. [31] showed a standard deviation (SD) of HbA_1c_ levels averaged across usual care and intervention groups being 1.2% at both baseline and after a 6-month intervention and a correlation of 0.4 between the two time points. We assume an SD of 1.2% in HbA_1c_ at Month 12 (primary endpoint) and a correlation of 0.2 between baseline and Month 12 measurements. In order to detect a mean difference of 0.5% between the usual care and DMP arms and 0.5% between the DMP and DMP plus financial incentive arms, with analysis of covariance (ANCOVA) adjustment for baseline HbA_1c_ and multiplicity adjustment by the closed testing procedure [32], a sample size of 90 per group is needed to have 80% power at a two-sided 5% familywise type 1 error rate. To allow for 20% attrition at Month 12, we will recruit 113 patients per arm, or 339 in total.

### Randomization

Participants will be randomized according to a 1:1:1 allocation ratio to the three arms, using stratified randomization with random permuted blocks within strata. The block size will be determined by a statistician generating the randomization list and will not be disclosed to the investigators and other study team members who have contact with study participants. Three stratification factors will be used: diabetes center (specialist clinic or polyclinic), gender, and dichotomized HbA_1c_ level at baseline (7.5–9.2% or 9.3–11.0%). For allocation concealment, sequentially numbered, opaque, and sealed randomization envelopes will be used for the randomization assignment for all participants.

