**Methods/design:**

TRIPOD is a randomized, open-label, controlled, multi-center, superiority trial with three parallel arms: (1) usual care only, (2) usual care with DMP, and (3) usual care with DMP plus M-POWER Rewards. A total of 339 adults with sub-optimally controlled T2DM (self-reported HbA_1c_ 7.5–11.0%) will be block randomized according to a 1:1:1 allocation ratio to the three arms. The primary outcome is mean change in HbA_1c_ level at Month 12 from baseline. Secondary outcomes include mean change in HbA_1c_ level at Months 6, 18, and 24; mean changes at Months 6, 12, 18, and 24 in weight, blood pressure, and self-reported physical activity, weight monitoring, blood glucose monitoring, medication adherence, diabetes self-management, sleep quality, work productivity and daily activity impairment, and health utility index; and proportion of participants initiating insulin treatment by Months 6, 12, 18, and 24. Incremental cost-effectiveness ratios will be computed based on costs per improvement in HbA_1c_ at Month 12 and converted to cost per quality-adjusted life year gained.

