### Objectives and hypotheses

#### Primary outcome and hypothesis

The objective of this study is to determine whether complementing usual care with the DMP, with or without financial rewards (M-POWER Rewards) can improve mean HbA_1c_ levels at Month 12 (primary endpoint) of individuals with T2DM.

We hypothesize that between baseline (date of HbA_1c_ test blood sample collection and randomization) and Month 12, mean improvements in HbA_1c_ level will be greatest in the DMP plus M-POWER Rewards arm, followed by DMP alone, followed by usual care.

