### Study setting and eligibility criteria

Adults (aged 21 to 70) with sub-optimally controlled T2DM from 11 Singapore Health Services (SingHealth) referral sites (two specialist diabetes centers and nine polyclinics) will refer themselves directly to the study team from Duke-NUS Medical School, who will manage and execute all study-related procedures, including the study visits (i.e., training sessions and follow-up assessments), at Duke-NUS Medical School or other study venues, if available. SingHealth is Singapore’s largest public healthcare group and is in a collaborative academic medicine partnership with Duke-NUS Medical School. Collectively, the SingHealth referral sites serve both low- and high-income patients, with all Singaporean citizens and permanent residents entitled to government subsidies. All eligibility criteria will be self-declared.

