#### Health outcomes

Measurements taken at the study visits will be recorded on hardcopy printouts. All data will be converted into electronic data using double data entry by two different individuals and verified for consistency. Any discrepancies will be resolved by referring to source documents. At the study visits, phlebotomists will verify participants’ identities before drawing blood and will label blood samples with the participants’ study IDs only. HbA_1c_ results will not contain any personal identifiers and will be shared with the study team after each batch of blood samples is processed.

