#### Primary analysis

Mean change in HbA_1c_ level at Month 12 is the primary outcome. The primary analysis will be performed on a modified intention-to-treat population, including participants who have both baseline and Month 12 HbA_1c_ level data. A linear regression model with HbA_1c_ level at Month 12 as the dependent variable and an intercept, HbA_1c_ level at baseline (continuous variable), indicator variables for participants who received DMP alone and participants who received DMP plus M-POWER, and indicator variables for stratification factors (gender and diabetes center) as independent variables will be performed. Using this model, a test for the global null hypothesis of all three arms having equal mean HbA_1c_ level at Month 12 will be performed (Null Hypothesis 1: Coefficient of DMP plus M-POWER = Coefficient of DMP = 0), followed by tests for three pairwise hypotheses, comparing mean HbA1c level at Month 12 in DMP alone vs. usual care (Null Hypothesis 2: Coefficient of DMP = 0), DMP plus M-POWER vs. usual care (Null Hypothesis 3: Coefficient of DMP plus M-POWER = 0), and DMP plus M-POWER vs. DMP alone (Null Hypothesis 4: Coefficient of DMP plus M-POWER = Coefficient of DMP). We will also conduct a sensitivity analysis with further adjustment for dichotomized HbA1c levels at baseline (7.5–9.2% vs. 9.3–11.0%). The differences in the primary outcome between study arms will be presented along with corresponding 95% confidence intervals. Following the closed testing procedure [32] for controlling for multiple comparisons involving three groups, only if tests of both the global null hypothesis and a pairwise null hypothesis reach statistical significance at the 0.05 level will the pairwise null hypothesis be rejected.

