If there are substantially different drop-out rates or different drop-out patterns among the three arms, a general linear model for repeated measures will be performed for the primary analysis. This model simultaneously models HbA_1c_ level at baseline, Month 6, and Month 12 as the dependent variables and includes interactions between indicator variables for DMP alone and Month 6 visit, DMP plus M-POWER and Month 6 visit, DMP alone and Month 12 visit, and DMP plus M-POWER and Month 12 visit as independent variables. The model will also adjust for visit (indicator variable for the Month 6 visit and indicator variable for the Month 12 visit) and randomization stratification variables (gender and diabetes center). An unstructured matrix will be used to model the residual variance-covariance structure within participant. The model does not include main effect terms for the intervention variables, and thus it constrains the estimated group means of baseline HbA_1c_ levels to be identical across the three randomized groups. This model specification helps control for the variation in baseline HbA_1c_ level arising by chance among the randomized groups. Using this model, a test for the global null hypothesis of all three arms having equal mean HbA_1c_ level at Month 12 will be performed (Null Hypothesis 1: Coefficient of interaction between indicator of DMP alone and indicator of Month 12 visit = Coefficient of interaction between indicator of DMP plus M-POWER and indicator of Month 12 visit = 0), followed by tests for three pairwise hypotheses, comparing mean HbA_1c_ level at Month 12 in DMP alone vs. usual care (Null Hypothesis 2: Coefficient of interaction between indicator of DMP alone and indicator of Month 12 visit = 0), DMP plus M-POWER vs. usual care (Null Hypothesis 3: Coefficient of interaction between indicator of DMP plus M-POWER and indicator of Month 12 visit = 0), and DMP plus M-POWER vs. DMP alone (Null Hypothesis 4: Coefficient of interaction between indicator of DMP alone and indicator of Month 12 visit = Coefficient of interaction between indicator of DMP plus M-POWER and indicator of Month 12 visit). If the missing data patterns do not necessitate using a general linear model for repeated measures as a primary analysis, this analysis will be conducted as a sensitivity analysis.

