#### Secondary effectiveness analyses

##### Quantitative outcomes

Secondary quantitative outcomes (weight, blood pressure, GPAQ total physical activity score, weight monitoring frequency, blood glucose monitoring frequency, diabetes medication adherence frequency, DSMQ sum score, global PSQI score, percent overall work impairment and percent activity impairment due to diabetes and related health problems using a modified WPAI:SHP, health utility index using 5-level EQ-5D) will be analyzed using a similar strategy as applied to the primary outcome. A linear regression model will be used to model the secondary quantitative outcome as the dependent variable and an intercept, the outcome at baseline (quantitative variable), indicator variables for participants who received DMP alone and participants who received DMP plus M-POWER, and indicator variables for stratification factors (gender, diabetes center, and dichotomized HbA_1c_ level at baseline) as independent variables. Additional analyses will also be performed to evaluate the intervention effects that account for insulin progression/medication changes and other potential effect modifiers, mediators, covariates, and program engagement metrics.

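### The HbA1c randomization stratum can only be the self-reported screening value, yet it carries the same "baseline" label as the laboratory covariate and is left out of the primary and repeated-measures models

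*Protocol article*

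**What the plan says.** All of the following is in the protocol article.

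- **Randomization** names three stratification factors: diabetes center, gender and "dichotomized HbA_1c_ level at baseline (7.5–9.2% or 9.3–11.0" percent.
- **Primary outcome and hypothesis** defines "baseline (date of HbA_1c_ test blood sample collection and randomization", so the baseline HbA1c is the study laboratory result from that day.
- **Participant timeline and study arms** places the blood draw and the disclosure of the arm in the same training session. **Participant retention** plans a single baseline visit.
- **Health outcomes** (data management) says HbA1c results "will be shared with the study team after each batch of blood samples is processed".
- The **Abstract** describes participants as having "sub-optimally controlled T2DM (self-reported HbA_1c_ 7.5–11.0" percent. **Study setting and eligibility criteria** adds "All eligibility criteria will be self-declared". **Inclusion criteria** allows the qualifying test to be up to 3 calendar months old.
- **Primary analysis** adjusts for continuous baseline HbA1c, gender and center. A sensitivity analysis adds "further adjustment for dichotomized HbA1c levels at baseline (7.5–9.2% vs. 9.3–11.0" percent. The repeated-measures alternative adjusts for "randomization stratification variables (gender and diabetes center" only.
- **Quantitative outcomes** adjusts for "stratification factors (gender, diabetes center, and dichotomized HbA_1c_ level at baseline". **Binary outcomes** uses the same three factors.

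**The concern.** One label, HbA1c at baseline, covers two measurements. One is the screening value that must be in hand when an envelope is chosen. The other is the laboratory value from blood drawn at the training session, which is known later. Someone programming the sensitivity or secondary models has a continuous variable with that name and an instruction to dichotomize it, and could reasonably cut the laboratory result. The indicator would then differ from the randomized stratum for some participants, and the two closed ranges would not say where a result such as 7.2% belongs.

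The lists of factors also disagree: three under Randomization and in the secondary models, two in the primary and repeated-measures models. Leaving the third out would make sense if it were a coarse version of the continuous covariate already in the model. It is not, because it is a different measurement taken at a different time.

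At stake are reproducibility and agreement between analysis and randomization. The validity of the primary comparison is not at stake.

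**Working it through.** **Step 1. Which HbA1c is available at randomization?**

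| Event | Timing | Section |
|---|---|---|
| HbA1c self-reported, test up to 3 months old | online screener, before the visit | Abstract; Inclusion criteria |
| Study team verifies medication and clinic from photographs | before the visit | Participant recruitment |
| Study blood drawn | training session | Participant timeline and study arms |
| Arm revealed | same session | Participant timeline and study arms |
| Laboratory HbA1c reaches the team | after batch processing | Health outcomes (data management) |

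No later baseline visit is planned. The only HbA1c described as known when the arm is revealed is the self-reported one. The strata, 7.5–9.2 and 9.3–11.0, together span exactly the self-reported eligibility range of 7.5–11.0.

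**Step 2. Which models contain the factor?**

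| Model | Continuous baseline HbA1c | Dichotomized HbA1c |
|---|---|---|
| Primary regression | covariate | absent |
| Sensitivity to primary | covariate | added |
| Repeated measures (may become primary) | first outcome | absent |
| Secondary quantitative | not listed (that outcome's own baseline is used) | listed as a stratification factor |
| Secondary binary | not listed | listed as a stratification factor |

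None of these sections says whether the indicator is as randomized or derived from the laboratory value.

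**Step 3. Is the sample size affected?** Inputs from Sample size: SD 1.2, correlation 0.2, difference 0.5, two-sided 5%, 80% power.

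- Residual SD = 1.2 × √(1 − 0.2²) = 1.176.
- n = 2 × (1.960 + 0.842)² × 1.176² / 0.5² ≈ 87 per group; 88 with the t distribution. The stated 90 gives power of about 0.81.
- 90 / 0.80 = 112.5, so 113 per arm, and 3 × 113 = 339, as stated.

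One more indicator costs one of more than 260 residual degrees of freedom, so the sample size stands.

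**Step 4. Precision gain from adding the as-randomized stratum.** Assumptions: the screening value, like the laboratory baseline, correlates 0.2 with Month 12 (the protocol's figure for baseline); the two HbA1c values correlate r = 0.4–0.8 with each other (not in the documents).

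- Extra R² = (0.2 − 0.2r)² / (1 − r²).
- r = 0.4: 0.12² / 0.84 = 0.017. r = 0.8: 0.04² / 0.36 = 0.004.
- Residual share without the stratum: 1 − 0.2² = 0.96. Reduction in residual variance: 0.017/0.96 = 1.8% and 0.004/0.96 = 0.5%.
- Reduction in standard error: about 0.9% and 0.2%. Dichotomizing makes it smaller still.

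**Step 5. Illustration if the laboratory value were cut instead.** The documents give no figure for agreement between self-report and laboratory, so these are assumptions: bivariate normal, SD 1.2 before truncation, source mean 8.0–9.0, correlation 0.4–0.9, self-report restricted to 7.5–11.0. Simulation gave 5.5–25% of participants (18–85 of 339) with a laboratory value outside 7.5–11.0, and 12–39% (42–132 of 339) on the other side of the 9.2/9.3 cut from their self-reported stratum. With closer agreement (SD of the difference 0.3–0.7, source mean 7.8–8.5, source SD 1.2–1.5) the ranges were 4–14% and 7–19%. If the indicator is as randomized, both figures are zero.

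**The case against.** A reader might infer that the analysis stratum is definitely not the randomized one and that participants with out-of-range laboratory values would drop out of the models. The documents do not support this. The secondary sections list the indicator among the stratification factors, beside gender and center. The cut-points repeat those under Randomization, and their outer limits equal the self-reported eligibility range. As-randomized use may well be intended, and then every participant has a category. Even if the laboratory value were cut, a split between 9.2 and 9.3 can place 7.2 or 11.3, so exclusion is speculation. A laboratory value from blood drawn before the intervention starts does not bias the comparison when used as a covariate.

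A reader might also infer that the primary standard errors are invalid without the third factor. That is too strong. Omitting a stratification factor generally makes standard errors slightly conservative, and the continuous laboratory baseline already takes up much of the same information.

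It can also be said that coding a stratum is work for the analysis plan, which the article promises before database lock. That would answer an omission. Here the article itself fixes the cut-points, defines baseline in a way the stratification cannot follow, and gives factor lists that disagree. These objections limit the size of the point but leave the inconsistency standing.

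**Conclusion.** The point holds as an inconsistency of definition and of covariate lists. On the stated sequence of events the stratum is the self-reported screening HbA1c. The article labels it as baseline, does not say which value the model indicator uses, and omits it from the primary model and from the repeated-measures model that may replace it.

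The consequence is modest. There is no bias, and sample size and power are unchanged. Adding the as-randomized stratum would lower residual variance by roughly 0–2%, given the protocol's correlation of 0.2 and an assumed range for the agreement between the two HbA1c values. The number of participants who would be misclassified or fall outside the ranges under a laboratory-based cut cannot be known from the documents; the percentages above only illustrate stated assumptions and apply to that reading alone. The main gain is an analysis that follows the randomization and that two programmers would code alike.

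**What to change.** 1. Under Randomization, state that the HbA1c stratification factor is the self-reported screening value used to select the envelope, and stop calling it the baseline level.
2. Use that as-randomized indicator, with gender and center, in the primary, repeated-measures, secondary quantitative and binary models. The sensitivity analysis that adds the dichotomized level is then no longer needed.
3. Keep the continuous laboratory baseline HbA1c as a separate covariate in the primary model and as the first outcome in the repeated-measures model.
4. Do not dichotomize the laboratory value. In the repeated-measures model it is already an outcome, so a cut of it would not be a sensible covariate, whereas the self-reported stratum is.

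The cost is a few sentences and one degree of freedom in the models that now omit the factor. No new data are needed, since the stratum has to be known to choose the envelope. The change should be made before arm assignments are disclosed to the statistician.

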### Participant recruitment, retention, withdrawal, discontinuation, and adverse event reporting

#### Participant recruitment

Eleven SingHealth referral sites (two specialist diabetes centers and nine polyclinics) will serve as referral sites for this study. Patients attending regular diabetes care at these referral sites will be recruited through various advertising avenues at the referral sites, newspaper advertising, and online sites. All recruitment materials will briefly explain the study design, list the key eligibility requirements, and direct interested participants to the study website that contains additional information about the study. The website will also contain contact information of the study team and serve as a means for interested patients to connect with the study team via a contact form. Interested patients may assess their eligibility by completing an online eligibility screener on the website, and prospective participants will be requested to provide their contact details and consent to be contacted. If the patient did not report having an HbA_1c_ level within the eligibility range or having taken an HbA_1c_ test within the past 3 calendar months, the patient will be presented with the option to have the study team arrange for the patient to retake the screener at a future date after the next regular, clinic-scheduled HbA_1c_ test has been taken. If a prospective participant answers “Yes” to any PAR-Q question [23], he/she will be required to provide an approval note from a physician to be able to participate in the study (conditional eligibility). Patients who answered “No” to all questions will be deemed physically fit to engage in physical activity as recommended in the DMP. The study team will contact all prospective participants to provide additional details about the study, answer any questions that patients might have, obtain photographs of the patients’ oral glucose-lowering drug to verify their medication and clinic, set up a unique personal link to complete the baseline questionnaire, and schedule a baseline training session. Prospective participants will attend training sessions at Duke-NUS Medical School (or other study venues, if available) where they will be briefed on the study, enrolled, measured for baseline values, recruited, and taught how to use the study devices, apps, and the M-POWER Rewards program. As an incentive to join the study and for compensation for their time, successfully recruited participants will receive SGD10 in cash at the end of the training session. Figure 2 illustrates the flow diagram for participants.
